#### Quarterly Assessments

QoL and mental health outcomes, including depression and generalized anxiety disorder, will be evaluated at baseline and 3, 6, 9, and 12 months. These assessments are designed to take approximately 5 minutes to complete.

#### Post Intervention Survey

Twelve months post-randomization, participants assigned to SAFE-CaPS will complete a structured online survey via REDCap to assess intervention engagement, usability, and changes in health behavior, based on the UTAUT framework. The survey will evaluate participants' responses to the 4 key intervention constructs: performance expectancy, effort expectancy, social influence, and facilitating conditions, along with their final behavioral intent.

#### Exit Interview

A subset of 30 intervention participants will be invited to participate in semistructured interviews and focus groups conducted via Zoom to collect qualitative data on the usability, engagement, and perceived benefits of the SAFE-CaPS app. The interview guide will explore several key domains related to participants’ experiences with the intervention. Specifically, the interviews will delve into their CaP survivorship journey, including interactions with health care providers, the long-term impact of treatment, and motivations for participating in the study. Questions will assess participants’ affective attitude (ie, feelings about the intervention), perceived effectiveness (ie, perceived improvements in health and well-being), and self-efficacy (ie, confidence in carrying out intervention-related behaviors). The domain of burden will capture perceived effort, challenges, and time investment associated with the intervention. Intervention coherence will assess how well participants understand the purpose and functioning of the app. Additionally, participants will be invited to offer recommendations for improvement, describe their ideal model of survivorship support, and share whether they would recommend the app to others facing similar experiences.

### Sample Size and Power Analysis

The sample size required to detect a significant change in the primary outcome (FACT-P Total Score) was estimated using a 2-sample *t* test. Although FACT-P will be assessed at baseline and at 3, 6, 9, and 12 months, the sample size calculation was based on detecting a statistically significant difference between groups at the 12-month timepoint, which serves as the primary endpoint. The calculation assumed a significance level (α) of 0.05, 80% power, and a 1:1 randomization ratio. Based on prior research by Cella et al [72], which reported an effect size between 0.39 and 0.58, the sample size was conservatively determined using the smaller effect size (0.39). Under these assumptions, a minimum of 105 participants per group is required to detect a meaningful difference in FACT-P scores.

We anticipate that 15% of the full sample will be lost to attrition; therefore, the final target sample size was set at 124 participants per group (N=248 total). A participant sampling plan will be implemented to ensure adequate representation of ethnic groups and balanced allocation across intervention and control conditions, in alignment with the randomized controlled trial design.

### Measures

This study will use a range of validated instruments and self-reported measures to assess key constructs related to QoL, symptom burden, psychosocial well-being, lifestyle behaviors, and health care access among Black men with CaP.

#### Primary Outcome

The primary outcome will be QoL, which will be assessed using the (FACT-P) questionnaire [72] at baseline, 3, 6, 9, and 12 months. FACT-P is a 39-item instrument that evaluates physical, emotional, and functional well-being, as well as CaP-specific concerns such as weight loss, appetite, pain, urinary symptoms, bowel function, and sexual health. Scores will be transformed onto a 0-100 scale, with higher scores indicating better QoL.

#### Secondary Outcomes

App engagement and usability will be evaluated based on frequency and duration of use, symptom-tracking interaction, and engagement with educational content. Technology acceptance and behavioral intent will also be assessed using the UTAUT framework, which evaluates performance expectancy, effort expectancy, social influence, and facilitating conditions. These outcome variables will be analyzed at multiple time points to determine the effectiveness of the SAFE-CaPS intervention in enhancing QoL, improving mental health, and supporting symptom self-management among Black survivors with CaP. Additionally, semistructured interviews and focus groups will be conducted to explore app usability, engagement, and perceived benefits.

#### Analytic Plan

The statistical analyses for the SAFE-CaPS study will include descriptive, bivariate, and multivariate methods to assess the intervention's impact on QoL, mental health, symptom management, and app engagement. Each variable will be examined for distribution, range, mode, median, and mean (SD). Skewness and kurtosis will be determined for all ratio-level variables, while frequency distributions will be calculated for nominal- and ordinal-level variables. Descriptive statistics will be used to summarize all study variables, and bivariate statistics will be computed to assess relationships among theoretical constructs.

Differences in demographic and clinical characteristics between the 2 groups will be analyzed using a 2-tailed independent *t* test, Fisher exact test, and the chi-square test. Intervention usage will be analyzed using descriptive and inferential statistics for the number of EMAs completed, alerts triggered, and views of the educational section. An adjusted linear regression mixed-effect model will assess the impact of treatment group assignment on FACT-P scores at 12 months, adjusting for relevant covariates such as age, socioeconomic status, treatment type, ethnicity, and cancer stage. Preliminary analyses will include checks for multicollinearity and score distributions to ensure model validity. The goal is to determine the effect of the intervention on QoL as measured by FACT-P, independent of these baseline characteristics.

Chi-square analyses and *t* tests will examine baseline differences between ethnic groups. One-way ANOVA and correlations will be conducted to determine whether demographic and clinical variables are significantly associated with perceived acceptability, accessibility, and engagement. Due to the preliminary nature of these analyses, only covariates significant at *P*<.05 will be included in the final models. Cronbach α will assess the reliability of the multi-item instrument to determine the internal consistency of the model used to measure the constructs of the proposed framework, as shown in Figure 3. A Cronbach α value ≥0.70 will be considered acceptable for internal consistency [73]. Data will be analyzed using SPSS (version 29; IBM Corp).

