**Methods:**

This 12-month stratified randomized clinical trial will enroll 248 Black survivors with CaP (including native born, African-born, and Caribbean-born men) into the SAFE-CaPS intervention arm and standard care (SC) control group (1:1 allocation). Eligible participants are self-identified Black men (including native born, African-born, and Caribbean-born) aged 40 to 80 years with a confirmed CaP diagnosis within the past 5 years who own or are willing to use a smartphone. SC will consist solely of routine oncology or primary care follow-up, including clinic visits, referrals, and supportive services as needed, with no digital components. The SAFE-CaPS intervention, developed using the Insight platform, includes daily and weekly ecological momentary assessments of pain, urinary and bowel symptoms, sleep, fatigue, sexual function, mood, physical activity, and diet; adaptive educational modules addressing treatment-related side effects and culturally grounded survivorship concerns; automated symptom alerts prompting nurse follow-up and provider notification; and engagement features such as reminders, goal-setting, and literacy-appropriate content. Intervention content incorporates culturally tailored messaging, patient narratives, and feedback from prior qualitative work with ethnically diverse Black CaP. Stratified randomization will ensure balanced representation of ethnic subgroups. Primary outcomes include overall QoL. Secondary outcomes include specific symptom domains, mental health (depression and anxiety), health care engagement, and app acceptability. Assessments will occur at baseline, 3, 6, 9, and 12 months, and linear mixed models with intent-to-treat principles will evaluate intervention effects over time.

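### The Analytic Plan words the primary FACT-P model as a mixed model of the 12-month score, names neither visit terms nor baseline FACT-P, and is not reconciled with the Abstract's model of effects over time

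*Protocol article*

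**What the plan says.** Three places in the protocol article bear on the primary analysis.

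- **Analytic Plan:** "An adjusted linear regression mixed-effect model will assess the impact of treatment group assignment on FACT-P scores at 12 months". The covariates are then given as an open list, with the model described as "adjusting for relevant covariates such as age, socioeconomic status, treatment type, ethnicity, and cancer stage". No visit term, arm-by-visit term or repeated outcome is mentioned, and baseline FACT-P is not among the named covariates. The next paragraph admits to the final models only covariates with P<.05. It follows a sentence about acceptability, accessibility and engagement, and does not say whether the rule also covers the FACT-P model.
- **Abstract, Methods:** "linear mixed models with intent-to-treat principles will evaluate intervention effects over time".
- **Sample Size and Power Analysis:** this section acknowledges all five FACT-P assessments but ties the sizing to one of them: "the sample size calculation was based on detecting a statistically significant difference between groups at the 12-month timepoint, which serves as the primary endpoint". The sizing method is a two-sample t test with no baseline adjustment.

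The Primary Outcome section confirms five FACT-P assessments, baseline included. The hypothesis in the Abstract and Introduction concerns greater improvement in quality of life.

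**The concern.** A mixed model needs something to be random over. With one 12-month score per man, a participant random effect cannot be separated from the residual, so the model as worded is ordinary regression. The Abstract's phrase could mean a slope, an average over follow-up or a set of visit-specific differences, and the article does not say which of these, if any, is primary.

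Two things are at stake if the Analytic Plan is followed to the letter.

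- **Precision.** Baseline FACT-P would naturally be expected to be the main predictor of later FACT-P, and it is already collected. Leaving it out gives a wider confidence interval than necessary.
- **Missing data.** A man who gives 3-, 6- or 9-month scores and then leaves contributes nothing to a regression on 12-month scores. The sample-size section anticipates 15% attrition, about 37 of 248 men (0.15 × 248 = 37.2). Strengths and Limitations names greater loss in the control arm as a possible risk. Excluding such men sits uneasily with the Abstract's intent-to-treat statement.

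**Working it through.** **Inputs from Sample Size and Power Analysis.** "The calculation assumed a significance level (α) of 0.05, 80% power, and a 1:1 randomization ratio"; standardised effect d = 0.39; "a minimum of 105 participants per group is required to detect a meaningful difference in FACT-P scores"; 15% attrition; 124 per group enrolled. Sidedness is not stated there. Two-sided is assumed because it reproduces the stated figure (one-sided gives 82 per group).

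**Input not in the document.** The correlation r between baseline and 12-month FACT-P. A range is shown.

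**1. The plan's own figure.**
- Normal approximation: n = 2(1.96 + 0.8416)² / 0.39² = 103.2, so 104 per group.
- Exact t test: 104.18, so 105 per group, as stated.
- Attrition: 105 / (1 − 0.15) = 123.5, so 124, as stated.
- Power with 105 per group: 80.3% (t) or 80.7% (normal).

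**2. Adding baseline FACT-P.** The residual SD falls by the factor √(1 − r²), so the effective effect size is 0.39 / √(1 − r²). With 105 per group, power ≈ Φ(0.39 × √(105/2) / √(1 − r²) − 1.96), where 0.39 × √52.5 = 2.826. The required n is 103.2 × (1 − r²), rounded up.

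| r | √(1 − r²) | Power, normal | Power, t | n per group for 80%, normal |
|---|---|---|---|---|
| 0 | 1.000 | 80.7% | 80.3% | 104 |
| 0.3 | 0.954 | 84.2% | 83.9% | 94 |
| 0.5 | 0.866 | 90.4% | 90.1% | 78 |
| 0.6 | 0.800 | 94.2% | 94.0% | 67 |
| 0.7 | 0.714 | 97.7% | 97.6% | 53 |

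The second column is also the ratio of confidence-interval widths. At r = 0.5 the adjusted interval is about 13% narrower.

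**3. Adding the interim visits.** A longitudinal model with a common baseline mean and arm effects at 3, 6, 9 and 12 months was evaluated with 124 per arm and dropout rising evenly to 15%. The quantity examined is the power of the 12-month contrast.

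- Equal correlation between all visits: 84.7% at 0.3, 91.0% at 0.5, 98.0% at 0.7. Baseline adjustment alone gave 84.2%, 90.4% and 97.7%, so the interim visits add less than one percentage point.
- Correlation decaying by visit (AR(1)), with adjacent-visit values of 0.3, 0.5 and 0.7: 81.0%, 81.5% and 84.1%. Here baseline and month 12 are four steps apart, so even 0.7 implies only 0.7⁴ = 0.24 between them. The formula in step 2 gives 82.9% at 0.24, so both sources of gain are small under this structure.

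**4. The comparator.** The 80% figure belongs to an unadjusted test, whereas the Analytic Plan already intends to adjust for five characteristics. If these explain part of the same variance, the further gain from baseline FACT-P is less than the table shows. The document gives nothing from which to calculate by how much.

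**The case against.** The strongest reply is that the Analytic Plan never says that 12-month scores are the only outcome data. It calls the model mixed-effect, the Abstract lists all five assessments and speaks of effects over time, and the sample-size section separates the assessment schedule from the 12-month endpoint. Together these are compatible with a repeated-measures model and a 12-month contrast. If baseline is one of the modelled visits, it need not appear as a covariate. The covariate list is open in any case, and a condensed article may leave model details to a fuller plan.

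Much of this stands. A reader might infer that the trial discards its repeated measures, or that baseline FACT-P is excluded. The documents support neither: the first is one possible reading, and the second variable is unnamed rather than ruled out. Nor is the trial underpowered against its own plan. Omitting baseline FACT-P also does not bias a randomised comparison; chance imbalance at baseline is part of the same precision loss. And differential loss is described as a potential limitation to be monitored, not as an expected result.

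What does not fall away is the wording. The one description of the FACT-P model in the Methods points to a single time point, the Abstract points to effects over time, and the text does not say how they fit together. This concerns what the article states, not detail it leaves elsewhere. Naming five covariates but not the baseline value of the outcome leaves the most useful one to be assumed.

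**Conclusion.** The point holds as an unreconciled description of the primary model and a missed gain in precision. It is not a demonstrated loss of planned power or a demonstrated bias.

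- If the Analytic Plan is followed literally, the analysis is a regression on men with a 12-month score. Men with only earlier follow-up scores drop out of it.
- The power forgone, relative to an unadjusted test, is about 4 percentage points at r = 0.3, 10 at 0.5 and 14 at 0.6. This rests on d = 0.39, 105 completers per arm, a two-sided 0.05 test and an assumed correlation. It is an upper guide, given the adjustment already planned, and it is small if correlation decays quickly between visits.
- The case for using the 3-, 6- and 9-month scores is mainly the handling of missing 12-month data, not power.

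**What to change.** In the Analytic Plan, state one primary model:

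- Outcome: FACT-P at all scheduled visits.
- Terms: arm, visit, arm-by-visit, ethnic stratum, and baseline FACT-P, entered either as a covariate or through a constrained common baseline mean.
- Primary contrast: the difference between arms at month 12, matching the sample-size section.
- Baseline FACT-P named as prespecified and exempt from any P<.05 covariate selection.

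Then reword the Abstract so that it describes the same model and contrast.

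The cost is wording. No new data are needed, the sample size need not change, and the mixed-model procedure in the planned SPSS software can fit the model. Results reports only 6 of 248 men enrolled, so the choice can be fixed before outcome data could influence it.

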### Study Randomization

This study will use a 1:1 stratified randomized controlled trial design and will enroll 248 participants who will be randomly assigned to either the SAFE-CaPS intervention group (n=124) or the control group (n=124) using REDCap’s stratified randomization module. Stratification will be based on ethnic background to ensure a balanced representation across study arms: native-born Black men (n=100), African-born Black men (n=74), and Caribbean-born Black men (n=74). Within each subgroup, participants will be randomized in equal numbers to the intervention and control arms (native-born Black men: 50/50; African-born Black men: 37/37; Caribbean-born Black men: 37/37). This stratified approach ensures balanced subgroup representation and supports exploratory analyses assessing potential differences in survivorship experiences and intervention response across ethnic backgrounds.

Due to the nature of the intervention, blinding of participants, care providers, and recruitment staff is not feasible. However, the data analyst will be blinded to group allocation to reduce analysis bias.

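### The P<.05 covariate screen, run against app acceptability, accessibility and engagement, is not limited to models of those outcomes and can be read to govern the FACT-P model

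*Protocol article*

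**What the plan says.** All the relevant statements on covariates are in the Analytic Plan section of the protocol article, in two consecutive paragraphs.

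- The first paragraph describes a mixed-effects model for the effect of assignment on FACT-P at 12 months, "adjusting for relevant covariates such as age, socioeconomic status, treatment type, ethnicity, and cancer stage". No significance condition is attached. The stated goal is the "effect of the intervention on QoL as measured by FACT-P, independent of these baseline characteristics".
- The second paragraph plans one-way ANOVA and correlations to "determine whether demographic and clinical variables are significantly associated with perceived acceptability, accessibility, and engagement". The next sentence calls these analyses preliminary and says that "only covariates significant at *P*<.05 will be included in the final models". The models are not named.

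Study Randomization makes ethnicity the only stratification factor: "Stratification will be based on ethnic background to ensure a balanced representation across study arms", with strata of 100, 74 and 74 men. Study Recruitment and Procedure says that control men have neither the app nor the EMAs. Post Intervention Survey gives the technology-acceptance survey to SAFE-CaPS men only, 12 months after randomisation.

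**The concern.** The selection rule has no stated scope, and the one model it could plainly act on is the primary one. Adjusting a between-arm comparison is useful when a covariate predicts the outcome, here FACT-P. This screen asks a different question: whether the covariate is related to how men rate or use the app. A covariate can be strongly prognostic for FACT-P and still fail it.

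If an analyst applied the rule to FACT-P, three things would follow. Post-randomisation data, largely from one arm, would decide the adjustment for both arms. The stratification factor would have to earn its place by a test unrelated to its purpose. And the covariate set of the primary model would stay unknown until the data had been examined, against the plan's own aim of an effect independent of the named characteristics.

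**Working it through.** **Which models does the rule reach?** In the Analytic Plan the word covariates occurs twice: in the FACT-P sentence and in the screening sentence. For acceptability, accessibility and engagement the section specifies ANOVA and correlations, and for usage only descriptive and inferential statistics in general terms. So FACT-P is the only covariate-adjusted model described, and its list is introduced as examples. On the other side, the screening sentence directly follows the acceptability tests in its own paragraph. Both readings are open.

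**The plan's own sample size.** Inputs from Sample Size and Power Analysis: effect size 0.39 SD, α 0.05 (taken as two-sided; the section does not say), power 80%, 15% attrition.

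- Normal approximation: n = 2(1.960 + 0.842)²/0.39² = 103.2, so 104 per arm.
- Two-sample t test: 104 per arm gives 79.9% power and 105 gives 80.3%, so 105.
- Attrition: 105/0.85 = 123.5, so 124 per arm, 248 in all.

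The stated figures reproduce. They rest on an unadjusted comparison.

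**How often would the screen keep a covariate?** For one unrelated to the screening outcomes:

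- one test: 5%;
- any of three independent tests: 1 − 0.95³ = 14.3%.

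Such a covariate is dropped 86% to 95% of the time. To pass a correlation test in the app arm, |r| must reach t/√(N − 2 + t²): 0.19 with 105 men, 0.18 with 124. A weak true correlation of 0.15 passes one test about 33% of the time.

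**What does dropping prognostic covariates cost?** Let R² be the share of FACT-P variance that the covariates explain. The documents give no value, so a range is assumed. Adjustment reduces the residual SD to √(1 − R²), and power ≈ Φ(0.39·√(105/2)/√(1 − R²) − 1.96).

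| Assumed R² | Residual SD | Power, prespecified adjustment | Power, covariates dropped |
|---|---|---|---|
| 0.05 | 0.975 | 82.6% | 80.7% |
| 0.10 | 0.949 | 84.6% | 80.7% |
| 0.20 | 0.894 | 88.5% | 80.7% |
| 0.30 | 0.837 | 92.2% | 80.7% |

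(80.7% is the normal-approximation counterpart of the 80.3% above.)

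**What if ethnicity is dropped?** With arms exactly balanced within strata, an analysis that ignores strata has type I error of about 2[1 − Φ(1.96/√(1 − R²))]: 4.4%, 3.9% and 2.8% for stratum R² of 0.05, 0.10 and 0.20.

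A simulation of 3,000 trials per setting used strata of 100/74/74, 1:1 allocation within strata, 15% random loss, and three independent screening outcomes in the app arm unrelated to stratum. The stratum was kept in 14% to 15% of trials.

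| Stratum R² | Power, screened | Power, always adjusted | Type I error, screened | Type I error, always adjusted |
|---|---|---|---|---|
| 0.05 | 81.8% | 82.8% | 4.8% | 5.4% |
| 0.10 | 82.3% | 84.6% | 4.1% | 4.9% |
| 0.20 | 82.8% | 87.7% | 3.2% | 4.4% |

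Monte Carlo standard errors are about 0.4 points for a 5% rate, √(0.05 × 0.95/3000), and 0.7 points for 82% power, √(0.82 × 0.18/3000).

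**The case against.** The strongest reply is that the screen was never meant for FACT-P. The FACT-P sentence comes first, in its own paragraph, names ethnicity, and carries no significance condition. The screening sentence calls the analyses just described preliminary, which most naturally means the acceptability, accessibility and engagement tests. The Analytic Plan opens by promising multivariate methods that cover app engagement, and the Results section anticipates exploratory analyses of app adoption, so the plural could refer to engagement models that a condensed article does not spell out. This stands as a fair reading. A reader might infer that the rule certainly governs the primary model and that ethnicity will be discarded; the text does not establish either.

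Two further points also stand in part. App use and the acceptance survey exist in one arm only, but the article also lists health care engagement as a secondary outcome, and engagement in the screening sentence could include it. And every R² above is assumed: what is lost is power beyond the plan, since the 80% was calculated without adjustment.

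The reply does not supply the missing scope. The sentence is a stated rule, not a detail left for later, and its wording places no limit on the models it covers.

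**Conclusion.** The point holds conditionally. The article states a significance screen with undefined scope, and the primary model's covariate list is open, so the rule can be applied to FACT-P. There it would test the wrong association and could remove the stratification factor.

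The size depends on how prognostic the covariates are. The power forgone runs from about 2 points at R² 0.05 (82.6% against 80.7%) to about 11 at R² 0.30 (92.2% against 80.7%), for covariates unrelated to the screening outcomes. It is small if they are only weakly prognostic. Dropping ethnicity makes the test somewhat conservative. It would be wrong to infer that the trial is underpowered or that type I error is inflated: power stays at or above the planned 80% in these scenarios, no inflation appears, and 105 and 124 per arm are unaffected.

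**What to change.** In the Analytic Plan, or in the SAP with a matching correction to the protocol:

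- State that the P<.05 screen does not apply to the FACT-P model or to any other between-arm model.
- Fit the FACT-P model with the list already named, closed rather than illustrative: age, socioeconomic status, treatment type, ethnicity and cancer stage, whatever their p-values. Keep ethnicity in every case as the randomisation stratum.
- Limit the ANOVA and correlation screen to exploratory analyses of acceptability, accessibility and engagement.

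The cost is wording and a few degrees of freedom out of about 210 analysed men (2 × 105). No new data are needed and the sample size does not change. The change is sound under either reading of the sentence. It can be made well before the outcomes are analysed: the article reports 6 men enrolled and places analysis in late 2027.
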